### Standard care

In line with standard clinical practice in the UK patients allocated to the standard care group will have no intensive care follow-up after hospital discharge. Patients will be followed-up for the trial outcome measures and end points only over the first year after hospital discharge. In line with good clinical practice, if there are concerns about the well being of these patients at trial follow-up, a GP letter will be generated.

### Procedure

#### Trial recruitment and baseline measurements

Patients will be approached in the period after ICU discharge and before hospital discharge, when their condition has been identified as stable and they are able to give informed consent. The local trial nurse will explain the trial and allow time for the patients to read an information sheet before seeking written informed consent. Patients will have baseline measurements recorded before allocation to their study group. Clinically-gathered data on patient demographics, ICU diagnosis, ICU stay, severity of illness using the Acute Physiology, Age and Chronic Health Evaluation (APACHE II) system [36], APACHE II co-morbidity score, ICU interventions and sedative use will be extracted from clinical audit data which is collected routinely during ICU stay in all units and available at time of enrolment. Also at baseline we will measure SF-36, EQ-5D, ICE score and HADS score before group allocation.

#### Allocation of participants to trial groups

After recruitment the patients will be randomised using the existing central automated computerised telephone randomisation service within the Centre for Healthcare Randomised Trials (CHaRT) in the Health Services Research Unit in the University of Aberdeen. Allocation will incorporate randomisation at baseline according to age, sex, HADS score, APACHE II, ICE questionnaire score and trial centre

#### Methods for protecting against other sources of bias

Due to the nature of the trial intervention, the nurses and doctors performing trial intervention cannot be blind to the trial group allocation. The researchers who measure trial end points and who will analyse the data will be blinded to the trial groups. To reduce bias, the principal outcome measures are questionnaires completed by participants at a time equivalent to three months after each clinic assessment. The analyses will be based on the 'intention to treat' principle including patients who cannot attend clinics due to psychiatric treatment.

#### Frequency and duration of follow up

Patients will be followed-up at six and twelve months for the patient-assessed measures of outcome. Postal questionnaires, rather than in-person assessment, have been chosen to avoid the six months outcome measurement acting as a trial intervention. This will also help to standardise the method of data collection.

#### Sample size

Previous studies performed in Aberdeen have shown a SF-36 mean physical component score (PCS) of 35 (S.D. 14) in ICU patients one year after ICU discharge (50 being the population norm). We have powered this study to detect a difference of 5 PCS points (0.36 SDs) increase in the clinic group compared to the standard care group (i.e. 35 to 40). For an unadjusted analysis, 123 patients per group would be required to detect this difference with 80% power and α of 0.05. However, data from previous studies in Aberdeen [2] indicate that the correlation between baseline, 3 month and 12 month SF-36 scores were at least 0.6. Such high correlations imply that the sample size could be reduced by 36% and the study would still detect a 5-point difference. Taking a more conservative estimate of 30% reduction in sample size, we would need 86 patients per group (172 total) to detect this difference with an 80% power at an α of 0.05. In practice, the power should be greater than 80% once the randomisation variables have been included in the statistical modelling. In our previous work we have found that 20% of patients who are discharged alive from hospital are lost to follow up/do not return questionnaires over the first year [2,6,8]. We will attempt to minimise this form of trial loss by keeping records of patients' telephone contact details as well as secondary contact names and addresses. All patients will be contacted by phone if they fail to return questionnaires and asked if they want to continue with the study. Nevertheless, we are assuming a 20% loss to follow-up and 20% mortality at 12 months; thus, the total number of patients to be recruited will be inflated to 135 per group or 270 in total.

#### Planned analyses

The outcomes will be compared between groups using generalised linear models which adjust for the randomisation factors. The model used will reflect the type of outcome data. For the primary outcome statistical significance will be at the 5% level (2P < 0.05) and 95% confidence intervals will be derived. *A priori *subgroup analysis will be undertaken for severity of illness (APACHE II), APACHE II co-morbidity, ICE score [8] and ICU length of stay. All subgroup analyses will seek stricter levels of significance (2P < 0.01). Data will be analysed using SPSS software.

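### The sample size assumes adjustment for baseline SF-36, but the stated analysis model names only covariates other than SF-36, so the 80% power is not secured as written

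*Protocol article*

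**What the plan says.** All references are to the protocol article.

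- **Sample size, target.** "We have powered this study to detect a difference of 5 PCS points (0.36 SDs) increase in the clinic group", with an SD of 14 for the 12-month physical component score (PCS).
- **Sample size, starting point.** "For an unadjusted analysis, 123 patients per group would be required to detect this difference with 80% power and α of 0.05".
- **Sample size, reduction.** Earlier Aberdeen data are said to show correlations of at least 0.6 between SF-36 scores at baseline, 3 months and 12 months, which would allow a 36% cut. The section then settles for less: "Taking a more conservative estimate of 30% reduction in sample size, we would need 86 patients per group (172 total".
- **Sample size, further gain.** After that cut, "the power should be greater than 80% once the randomisation variables have been included in the statistical modelling".
- **Allocation of participants to trial groups.** Randomisation is "according to age, sex, HADS score, APACHE II, ICE questionnaire score and trial centre".
- **Trial recruitment and baseline measurements.** "Also at baseline we will measure SF-36, EQ-5D, ICE score and HADS score before group allocation".
- **Planned analyses.** "The outcomes will be compared between groups using generalised linear models which adjust for the randomisation factors". Baseline SF-36 is not mentioned in this section.

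**The concern.** The cut from 123 to 86 per group is the usual analysis-of-covariance saving: a covariate that correlates at r with the outcome multiplies the residual variance by 1 − r². The saving comes from the model, not from the correlation alone, so the earlier SF-36 score has to be in the model. Follow-up is planned at six and twelve months, so no 3-month score will exist, and a score taken after randomisation would not be a baseline covariate anyway. Baseline SF-36 is the only available source of the saving.

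The randomisation factors cannot be read as including SF-36. Their list omits it, and the sample size section counts them as a gain on top of the SF-36 reduction. Planned analyses thus states the extra adjustment and does not state the one that justified the smaller trial.

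An analyst who follows Planned analyses literally would fit a model less precise than the one the sample size presumes, and a true 5-point benefit could be missed more often than the planned 20%. If the covariate set is settled only after the data are seen, two defensible primary models exist, and they may give different p-values.

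**Working it through.** **Inputs**
- Difference 5 PCS points, SD 14, 80% power, 86 analysed per group, correlation 0.6, 20% loss and 20% mortality: Sample size.
- Two-sided 5% significance: Planned analyses.
- Equal groups: 135 per group, Sample size.
- R² is the share of 12-month PCS variance explained by the model covariates. **Assumed range**; the article gives no value for the randomisation factors.

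**Step 1: reproduce the plan's figures**
- Unadjusted n per group = 2 × (1.960 + 0.842)² × (14/5)² = 123.07. Stated: 123.
- Saving at r = 0.6: 1 − r² = 1 − 0.36 = 0.64, a 36% cut. Stated: 36%.
- Applied cut: 123 × 0.70 = 86.1. Stated: 86.
- Inflation: 86 / (0.8 × 0.8) = 134.4, rounded up to 135 per group, 270 in total. Stated: the same.

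The arithmetic is sound. It corresponds to a model whose covariates explain 30% of the outcome variance.

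**Step 2: power at 86 per group by variance explained**

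Power = Φ( 5 / [14 × √(1 − R²) × √(2/86)] − 1.960 )

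With R² = 0 the standard error is 14 × √(2/86) = 2.135, so power = Φ(5/2.135 − 1.960) = Φ(0.382) = 64.9%. A t-based calculation gives 64.4%.

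| R² | Standard error | Power |
|---|---|---|
| 0 | 2.135 | 64.9% |
| 0.10 | 2.025 | 69.5% |
| 0.20 | 1.910 | 74.5% |
| 0.30 | 1.786 | 79.9% |
| 0.36 (baseline SF-36, r = 0.6) | 1.708 | 83.3% |

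**Step 3: detectable difference**

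With R² = 0, the difference detectable with 80% power is (1.960 + 0.842) × 2.135 = 5.98 points, against the planned 5.

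**Step 4: compare the covariate sets**

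| Section | Covariates |
|---|---|
| Sample size | Baseline SF-36 (for the 30% cut), then the randomisation variables as an extra |
| Planned analyses, with the list under Allocation | Age, sex, HADS, APACHE II, ICE score, centre |

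The second set lacks the one covariate on which the first set's figure depends.

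**The case against.** The best reply is that the authors did intend baseline adjustment. The sample size section contrasts an unadjusted analysis with a reduced one, then speaks of adding the randomisation variables, which reads naturally as a model that already holds baseline SF-36. The score is collected before allocation. Planned analyses is a short paragraph in a journal article, and a full covariate list is often left to the full protocol or SAP, neither of which is shown.

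Much of this stands, and it rules out three stronger readings:

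- **That the analysis adjusts only for the randomisation factors.** A reader might infer this, but the text contains no such restriction and nowhere excludes baseline SF-36.
- **That the 80% power is not delivered.** This needs baseline SF-36 to be actually omitted and the randomisation factors to explain less than about 30% of the PCS variance. The article establishes neither. The 65% figure is the extreme case in which six factors together explain nothing; at R² = 0.20 the miss rate is about 25.5%, not far above 20%.
- **That the trial is too small.** With no covariate gain, 123 / 0.64 = 192.2, so 193 per group would have to be recruited instead of 135. That applies only if the adjustment is forgone, and nothing requires that.

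The appeal to an unseen SAP does not remove the point. Planned analyses is not silent on covariates: it states a set, and that set differs from the one the power calculation requires. An SAP written from that wording would carry the mismatch forward.

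**Conclusion.** The point holds as a mismatch between two sections of the same document. The sample size rests on a primary analysis adjusted for baseline SF-36, and the stated model does not name that covariate, so the 80% power is not secured by the model as written.

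The possible loss is conditional. If baseline SF-36 is left out, power for a 5-point PCS difference runs from about 65% to 80% as the variance explained by the randomisation factors runs from 0 to about 0.30. That range is an assumption. The figures also assume SD 14, a two-sided 5% test and 86 analysed per group, and they concern the PCS, the score on which the trial was powered. With baseline SF-36 in the model at the stated correlation, power is 83% before any gain from the randomisation factors, and the planned 80% is met.

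**What to change.** In Planned analyses, state that each 12-month SF-36 component score will be compared between groups by a linear model adjusting for the baseline value of that same component score in addition to the randomisation factors. If the SAP already says this, align the protocol wording with it. The choice should be fixed before the outcome data are seen.

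The cost is one sentence. Baseline SF-36 is already collected before allocation, so no new data are needed and the recruitment target of 270 stays as it is. The way the randomisation factors themselves enter the model need not change to resolve this point.

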#### Economic issues

A formal economic evaluation is an integral part of this project. Cost per participant for each arm of the trial will be calculated. An estimate of primary and secondary care resource utilisation per patient will be made using patient questionnaires and review of hospital notes over the first year after hospital discharge. Unit costs/prices will be obtained using published estimates for health care services and/or interventions as well as study specific estimates [37-39]. QALYs will be calculated using the area under the curve method. For this, EQ-5D questionnaire responses will be valued using UK population tariffs [33]. The estimation of QALYs will take account of the mortality of study participants. Participants who die within the follow-up period will be assigned a zero utility weight from their death to the end of the follow-up. QALYs before death will be calculated using linear extrapolation between QALY scores. Point estimates for mean costs and mean QALYs will be derived for treatment and control groups to obtain Incremental Cost per QALY gained. Measures of variance of outcomes are likely to involve bootstrapping estimates for costs and QALYs. Results will be presented using Cost Effectiveness Acceptability Curves (CEACs). Deterministic and probabilistic sensitivity analysis will be developed to address different types of uncertainties within the economic evaluation such as differences in death rate. An element of this sensitivity analysis will be to explore the impact of extrapolating to a longer time than that afforded by the trial. This will be informed by previous research in which we have been involved [2,6,8], and will use a variety of modelling techniques. Subgroup analysis will follow the subgroup definitions within the trial.

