#### Secondary measures

HR-QOL will be assessed at six months after ICU discharge. Quality-adjusted life years (QALYs) using EQ-5D [33]; incidence and severity of posttraumatic psychopathology as measured by Davidson Trauma Scale (DTS); anxiety and depression using Hospital Anxiety and Depression Scale (HADS) will be assessed at both six and twelve months. Contacts with health services measured as part of the economic analysis; patient satisfaction will be assessed at twelve months using a patient satisfaction survey; primary and secondary health care costs in the year after hospital discharge, and mortality in the twelve months after ICU discharge. All non-clinic interventions will be monitored and documented. These data will be collected from hospital case notes review and patient questionnaires.

The EQ-5D assesses five attributes of quality of life, namely mobility, self-care, usual activity, pain/discomfort, and anxiety and depression [2]. An overall single score is obtained which can then be converted into a utility score. The DTS [34] will assess posttraumatic psychopathology and the HADS [35], anxiety and depression. Both the DTS and HADS have been validated in this patient population [6,9,16,19]. The DTS has been used widely in the initial assessment of patients at risk of posttraumatic stress disorder (PTSD). It measures all core symptoms of PTSD i.e. intrusion, avoidance and hyperarousal and has a 'cut-off' score of 27 or more that indicates significant posttraumatic psychopathology whilst a score of 40 or more indicates a likely diagnosis of PTSD [34]. The HADS questionnaire contains 14 statements and scoring results in scales of 0–21 for anxiety and depression respectively. Scores of 8–10 indicate the possibility of anxiety or depression, and 11 and above indicate that these are likely to be present.

The Intensive Care Experience Questionnaire (ICE) will be used to assess patients' perceptions of their experience [8]. This measure assesses four aspects of such an experience – 'awareness of surroundings', 'frightening experiences', 'recall of experiences', and 'satisfaction with care'. Previous work has demonstrated its association with both short and long-term psychological outcome [8], and we have used the median value from the 'frightening experiences' aspect as the score for the randomisation procedure.

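### The cost per QALY rests on group mean QALYs with no stated adjustment for baseline EQ-5D, so chance baseline differences partly carry over and precision is lost

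*Protocol article*

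**What the plan says.** Economic issues sets out how the QALYs are built, "QALYs will be calculated using the area under the curve method", and how the ratio is formed: "Point estimates for mean costs and mean QALYs will be derived for treatment and control groups to obtain Incremental Cost per QALY gained". It covers tariffs, the handling of deaths, bootstrapping and acceptability curves, but names no covariate for the QALY comparison.

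Baseline utility will be available: "Also at baseline we will measure SF-36, EQ-5D, ICE score and HADS score before group allocation". The later points on the curve come from the postal questionnaires: "Patients will be followed-up at six and twelve months for the patient-assessed measures of outcome".

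Two other sections bear on the point. Secondary measures lists "Quality-adjusted life years (QALYs) using EQ-5D" as an outcome, and Planned analyses says: "The outcomes will be compared between groups using generalised linear models which adjust for the randomisation factors". The factors are given under Allocation of participants to trial groups: "Allocation will incorporate randomisation at baseline according to age, sex, HADS score, APACHE II, ICE questionnaire score and trial centre". Baseline EQ-5D is not among them.

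**The concern.** A QALY computed over the trial year contains the baseline utility as its starting point. If one arm happens to start with better utility, its mean QALY is higher even when treatment does nothing. The gap grows because patients who start better tend to stay better. A difference in group means credits that gap to the follow-up programme, or charges it against it.

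Cost-effectiveness is one of the trial's stated aims. The denominator of the incremental ratio may be small, so a shift of a few hundredths of a QALY can change the ratio noticeably. At a willingness-to-pay threshold λ, a shift of d QALYs moves incremental net benefit by λ × d, and the acceptability curve moves with it. Variation that baseline could have explained also stays in the standard error.

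The article accepts this principle for its primary outcome. Sample size relies on baseline-to-follow-up SF-36 correlations of at least 0.6 to reduce the required number per group.

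**Working it through.** **The plan's own figures.** No figure is given for QALYs. The sample size does reproduce:
- Unadjusted: 2 × (14 × (1.960 + 0.842)/5)² = 123.07, stated as 123 per group.
- Baseline credit: 123 × 0.70 = 86.1, stated as 86.
- Losses: 86/(0.8 × 0.8) = 134.4, stated as 135.

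The last figure supplies the 135 per arm used below.

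**Weights.** Take baseline as month 0 (it is in fact recorded between ICU and hospital discharge) and assess at 6 and 12 months. Then

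QALY = 0.5 × (u0 + u6)/2 + 0.5 × (u6 + u12)/2 = 0.25 u0 + 0.50 u6 + 0.25 u12.

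**Assumptions, none from the article.** The EQ-5D SD is 0.2 to 0.4, the same at each time. The correlation r between any two times is 0.3 to 0.6.

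**Size of a chance imbalance.** SE of the baseline difference = SD × √(2/135): 0.0243, 0.0365 and 0.0487 for SD 0.2, 0.3 and 0.4.

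**Carry-over before deaths.** The slope of QALY on baseline is 0.25 + 0.50r + 0.25r = 0.25 + 0.75r. It is 0.475 at r = 0.3 and 0.70 at r = 0.6. The weight alone contributes 0.25.

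**Precision before deaths.** Var(QALY)/SD² = 0.375 + 0.625r, so R² = (0.25 + 0.75r)²/(0.375 + 0.625r).
- r = 0.3: 0.2256/0.5625 = 0.401. SE reduction = 1 − √0.599 = 23%.
- r = 0.6: 0.490/0.750 = 0.653. SE reduction = 1 − √0.347 = 41%.

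**With deaths.** Sample size assumes 20% mortality, and Economic issues sets utility to zero after death. A simulation of one million patients per scenario used normal utilities and 20% deaths at uniform times, independent of baseline. Mean utility was 0.4 at baseline and 0.6 at follow-up:

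| SD | r | Slope | Shift, 1 SE | Shift, 1.96 SE | R² | SE cut, 1 − √(1 − R²) |
|---|---|---|---|---|---|---|
| 0.2 | 0.3 | 0.439 | 0.0107 | 0.0210 | 0.200 | 11% |
| 0.2 | 0.6 | 0.636 | 0.0155 | 0.0303 | 0.360 | 20% |
| 0.3 | 0.3 | 0.439 | 0.0160 | 0.0315 | 0.275 | 15% |
| 0.3 | 0.6 | 0.635 | 0.0232 | 0.0455 | 0.469 | 27% |
| 0.4 | 0.3 | 0.440 | 0.0214 | 0.0420 | 0.318 | 17% |
| 0.4 | 0.6 | 0.636 | 0.0310 | 0.0607 | 0.526 | 31% |

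With means of 0.5 and 0.65 the slopes are essentially the same. The lowest R² is then 0.183, a cut of 10%.

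**Scale.** The article says: "We have powered this study to detect a difference of 5 PCS points (0.36 SDs) increase in the clinic group". Suppose, purely for illustration, that 0.36 SD also applied to EQ-5D at both follow-ups with SD 0.30. The gain before deaths would be 0.36 × 0.30 × (0.50 + 0.25) = 0.081 QALY. The matching one-SE shift before deaths is 0.0365 × 0.475 = 0.017 to 0.0365 × 0.70 = 0.026, or about 21% to 32% of that gain.

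**The case against.** The strongest reply is that the article is a condensed account. Its economic section is an outline, and the covariates of a QALY regression often appear only in a full analysis plan. Nothing in the section is contradictory or numerically wrong. It also never calls the means raw or unadjusted, and regression-adjusted means would fit the sentence. A reader might infer that the plan commits to unadjusted means, but the text does not go that far.

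In addition, QALYs are a listed secondary outcome, so the general models can be read as covering them. Adjustment for HADS, which overlaps with the anxiety and depression item of EQ-5D, and for the other factors would then absorb part of any imbalance. If the factors explained 30% of baseline EQ-5D variance (an assumption), the SE of the remaining imbalance at SD 0.30 would be 0.0365 × √0.70 = 0.031.

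Much of this stands, and it limits the claim. It does not remove it. The article does state how the ratio is formed, and under either reading baseline EQ-5D has no role. HADS does not measure mobility, self-care, usual activities or pain.

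A reader might also infer that the comparison is biased, or that a baseline difference passes through in full. Neither is supported. Under randomisation the difference in means is unbiased, and a bootstrap of it already reflects chance baseline variation. The carry-over is also well below 1.

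**Conclusion.** The point holds as a matter of efficiency and of protection against chance imbalance. As described, neither the incremental ratio nor the general models adjust QALYs for a baseline measurement that is part of the QALY itself. Allowing for 20% deaths, about 0.44 to 0.64 of a baseline EQ-5D difference would reach the incremental QALYs: 0.011 to 0.031 QALY for a one-SE imbalance and 0.021 to 0.061 for a 1.96-SE imbalance. Adjustment would reduce the standard error of the QALY difference by about 10% to 31%.

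These sizes rest on the assumed SD and correlations, on deaths independent of baseline, and on all 135 per arm contributing. They are upper-end figures if the randomisation factors are already adjusted for, since those factors would take up some of the same variation. The primary SF-36 comparison is not affected.

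**What to change.** State in Economic issues that incremental QALYs will be estimated by regressing each patient's QALY on treatment arm, baseline EQ-5D utility and the randomisation factors. Refit that regression, jointly with the cost comparison, within each bootstrap resample that feeds the incremental ratio and the acceptability curves, so that the intervals gain the precision too. Keep the unadjusted difference as a sensitivity analysis.

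The cost is a sentence or two and a few lines of code. No new data are needed. Fixing it before the data are seen also means that the choice to adjust cannot depend on the imbalance observed.
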